#### Primary effectiveness outcome

Self-reported time (hours/week) spent in planned physical activity over the last 7 days at 6 months from baseline. This will be measured using the planned activity subscale of the Incidental and Planned Exercise Questionnaire (IPEQ). The self-report IPEQ has excellent psychometric properties and assesses the level of physical activity relating to both basic and more demanding activities [44]. Planned physical activity includes total time spent participating in exercise classes, home exercise, other sport or physical recreation activities, and walking for exercise.

#### Primary implementation outcome

The primary implementation outcome is reach, defined as the proportion of eligible new physiotherapy patients who receive brief physical activity counselling within routine physiotherapy care, measured from a checklist completed by the physiotherapists.

#### Secondary effectiveness outcomes

##### IPEQ_total

The total physical activity (planned and incidental) will be measured using the total time in hours/week self-reported using the IPEQ. The total physical activity includes the total time spent participating in planned physical activity as well as other walks, outside gardening and maintenance and time on feet indoors.

##### Average step count per day

This is measured using Actigraph accelerometer model GT3X *(Pensacola FL USA).* The Actigraph GT3X is a non-invasive tri-axial accelerometer. Participants will be instructed to wear the accelerometer for 7 consecutive days during waking hours (except during water activities or bathing). Daily step count will be averaged over valid weartime days (≥10 h per day) to give average steps per day as the variable of interest. This measure will only be collected for a sub-sample of the patient participants due to resources and as a way of testing the feasibility of device-based physical activity measurement for future scale-up studies.

##### Patient-Reported Outcomes Measurement Information System (PROMIS-29 v2)

The PROMIS-29+2 Profile v2.1 will be used to assess the physical functioning and mental wellbeing of participants. The PROMIS-29 includes a numeric rating (0 to 10) pain intensity scale and seven health domains (physical function, anxiety, depression, fatigue, sleep disturbance, participation in social roles and activities, and pain interference) each rated on a 5-point scale. Additionally, participants will be asked to answer two items from Cognitive Function – Abilities (PC6r and PC27r), so preference-based scores can be calculated [45, 46]. Seven domain scores, a pain intensity score and physical and mental health summary scores will be generated (raw and T-score) with preliminary evidence supporting the reliability and validity of this tool [47].

##### EuroQOL-5D (EQ5D-5L)

Utility-based quality of life will be measured using the EQ5D-5L, a 5-item quality of life scale measuring the domains of mobility, self-care, usual activities, pain or discomfort and anxiety or depression, each rated on a 5-point scale ranging from no problems with that domain to extreme problems or unable to do that domain. In addition, there is a visual analogue scale from 0 to 100 to indicate their current health status, with zero being the worst imaginable health status and 100 being the best imaginable health status. The EQ5D-5L provides five domain scores, visual analogue scale score (0 to 100) and overall health utility score [48, 49].

##### Barriers to Physical Activity Questionnaire for People with Mobility Impairments (BPAQ-MI)

Barriers to participation in physical activity will be measured using the BPAQ-MI [50]. This scale measures barriers to physical activity across the intrapersonal, interpersonal, organisational, and community domains and has shown good test-retest reliability and construct validity [50]. This scale lists 63 potential barriers within eight domains (health, beliefs/attitudes towards physical activity, friends, family, facility-built environment, staff/program/policy, community-built environment and safety) for the responder to identify barriers limiting their participation in physical activity. Any reported barrier is rated on a 5-point scale as to how limiting it is. Each barrier has an item weighting which is multiplied by the score for that barrier between 0 and 5. The eight domains and total scores are calculated.

##### Healthcare evaluation

A study-specific questionnaire will collect information on the participant’s impressions of their health care. Specifically, it will ask if they received advice about physical activity from their physiotherapist or other healthcare providers and if they experienced any adverse events while participating in physical activity over the last 6 months.

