#### Patient inclusion criteria

Patients will be recruited by the participating physiotherapists in each of the 30 clusters. Patient participants are likely to be affected by common and/or burdensome conditions such as, but not limited to, osteoarthritis, lower limb amputations, chronic pain, stroke, brain injury, cardiac and pulmonary disease. Patients will be eligible if they are at least 18 years old, are new patients of one of the participating physiotherapists during the recruitment period, live in the community (as opposed to residential care), able to leave their home without physical assistance from another person but may use a walking aid or wheelchair (anticipated within 6 months of recruitment), are without major cognitive impairment (e.g., diagnosis of dementia), do not have any medical reasons for which interventions aimed at increasing physical activity would be contra-indicated and have sufficient language capabilities to respond to written questionnaires in English, Arabic or Vietnamese.

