### Data collection methods and outcome measures

As a hybrid type II study [29], patient-level effectiveness and implementation outcomes will be measured. All effectiveness outcomes (excluding device-measured physical activity and impressions of physiotherapy) as well as demographic information and co-morbidities will be assessed at baseline to enable a description of the patient-participant’s baseline characteristics and to obtain values to enter as covariates in the models comparing groups at follow-up. At the time of consent, the treating physiotherapist will provide the participant with a copy of the paper-based survey. This will be completed independently by participants or assisted by study staff over the telephone who are blinded to physiotherapy team allocation. At 6 months post-baseline, follow-up paper-based surveys will be mailed to participants and followed up by blinded research staff if surveys are not returned by mail.

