### Data analysis and management

#### Sample size

The sample size calculation was undertaken in STATA 14.2 using the “clustersampsi” command. Recruitment of 300 patients undergoing physiotherapy is sufficient to detect a 1.5-h between-group difference in the self-reported time spent in planned physical activity per week, estimated at 3 h/week (SD 4.4 hours/week) (waitlist control group) to 4.5 h/week (immediate-implementation group) (a between-group difference found to be achievable in our previous study [58]). All calculations used 80% power, alpha = 0.025 (to account for co-primary outcomes), 15 clusters per arm, average cluster sizes of 10, baseline-covariance 0.6 and intracluster correlation 0.05. This sample size will also be sufficient to detect an absolute 25% difference in the proportion of eligible patients receiving brief physical activity counselling within routine physiotherapy care (primary implementation outcome (reach), 35% in the waitlist control group and 60% in the immediate-implementation group).

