##### Patient-level effectiveness outcomes

The primary analysis will evaluate the effect of the multi-faceted implementation strategy to train, support and facilitate physiotherapists to deliver brief physical activity counselling as part of their routine care [targeted at the cluster level] on primary and secondary effectiveness outcomes. The main (intention-to-treat (ITT)) dataset analysed will be constituted of all patients recruited into the study irrespective of what amount of physical activity counselling they received from their treating physiotherapist. For the continuous outcomes, multiple linear regression will be used with a group (immediate-implementation vs. waitlist control) as the primary independent variable and baseline scores as a covariate. Binary logistic regression will be used to compare groups on dichotomous outcome measures with the group as the primary independent variable.

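### The only labelled adverse event outcome is described as counting events during physical activity, so net harm cannot be compared between arms from it

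*Protocol article*

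**What the plan says.** The adverse event item is in the protocol article, Secondary effectiveness outcomes, Healthcare evaluation. The instrument is introduced with "A study-specific questionnaire will collect information on the participant’s impressions of their health care", and one of its questions is "if they experienced any adverse events while participating in physical activity over the last 6 months". No other part of the article names adverse events.

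Four other places bear on it:

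- **Baseline.** Data collection methods and outcome measures states "All effectiveness outcomes (excluding device-measured physical activity and impressions of physiotherapy) as well as demographic information and co-morbidities will be assessed at baseline". The item belongs to the impressions questionnaire, so it appears to have no baseline value.
- **Analysis.** Patient-level effectiveness outcomes states "Binary logistic regression will be used to compare groups on dichotomous outcome measures with the group as the primary independent variable". No exposure term is mentioned.
- **Expected activity.** Sample size gives planned activity as "estimated at 3 h/week (SD 4.4 hours/week) (waitlist control group) to 4.5 h/week (immediate-implementation group").
- **Population.** Patient inclusion criteria names, as examples, "osteoarthritis, lower limb amputations, chronic pain, stroke, brain injury, cardiac and pulmonary disease".

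Other data could reveal harm. Healthcare utilisation collects hospital admissions, emergency visits and outpatient contacts in both groups over the 6 months, for costing. PROMIS-29 and EQ5D-5L record pain, as effectiveness outcomes. None of these is designated as safety data.

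**The concern.** Whether an event counts depends on what the patient was doing when it happened, and activity time is what the strategy is meant to change after randomisation. Two consequences follow.

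First, the item is incomplete in a way that matters for this comparison. Taken literally, a pain flare the next day, an overuse injury that builds up, or a later cardiac or respiratory event is not counted even if activity caused it. These are plausible in the conditions listed. A fall at home during inactive time is not counted either, and greater activity might make such falls fewer. This gap needs no assumption about event rates.

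Second, the item tends to rise with hours of activity even when an hour of activity is no more dangerous in one arm than in the other.

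At stake is the reading of the harms result. An excess in the immediate arm could go with fewer events overall, and equal proportions could hide an excess of delayed harm.

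**Working it through.** **1. The plan's own figure.** Inputs from Sample size: difference 1.5 h/week, SD 4.4, 80% power, alpha 0.025 (two-sided assumed), 15 clusters per arm, average cluster size 10, intracluster correlation 0.05, and 0.6 read as the baseline correlation.

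- SD after baseline adjustment: 4.4 × √(1 − 0.6²) = 3.52
- Patients per arm before clustering: 105
- Design effect: 1 + (10 − 1) × 0.05 = 1.45
- Total: 2 × 105 × 1.45 = 304.5, against 300 stated. Power at 150 per arm is 79.5%.

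The sample size reproduces, so 3 against 4.5 h/week is the contrast the trial was sized on.

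**2. Dependence on activity time.** The documents give no event rate, so the control proportion p₀ is assumed. With a constant risk per hour, equal in both arms, and R the ratio of activity hours, the proportion with at least one event in the immediate arm is p₁ = 1 − (1 − p₀)^R.

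If only planned activity counts, R = 4.5/3 = 1.5:

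| p₀ | p₁ | Odds ratio |
|---|---|---|
| 5% | 7.4% | 1.52 |
| 10% | 14.6% | 1.54 |
| 20% | 28.4% | 1.59 |

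**3. How far that depends on R.** The item refers to physical activity, not planned activity. The IPEQ total described in the article also includes other walks, gardening and time on feet indoors. If I hours/week of incidental activity (assumed, unchanged by the strategy) count as well, R = (4.5 + I)/(3 + I):

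| I (h/week) | R |
|---|---|
| 5 | 1.19 |
| 10 | 1.12 |
| 20 | 1.07 |
| 30 | 1.05 |

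At R = 1.1 and p₀ = 10%, p₁ = 1 − 0.9^1.1 = 10.9%.

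The 1.5 h/week gap is also a month-6 value. If both arms start at 3 h/week and the immediate arm rises linearly to 4.5, its average is 3.75, so R = 3.75/3 = 1.25 and p₁ = 12.3%.

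**4. Would a test pick it up?** With 150/1.45 ≈ 103 effective patients per arm, two-sided 0.05 and R = 1.5, power is about 11%, 17% and 29% at control proportions of 5%, 10% and 20%. A false alarm from a significance test is not the main worry. The worry is what the estimate means.

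**5. What the item cannot show.** In the 10% against 14.6% case, the item shows an excess of 14.6 − 10 = 4.6 percentage points. If events outside activity fell by about the same 4.6 points (ignoring patients with both kinds), total events would be equal in the two arms. The item would read the same whether or not that fall occurred.

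**The case against.** The strongest reply has four parts.

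- **The wording is a summary.** The article describes the questionnaire in indirect speech. The item itself, any follow-up questions and any fuller adverse event procedure are not shown. This stands, so the point is about the outcome as described, and the first step is to check the actual form.
- **Extra events from extra activity are a real effect.** Under intention to treat, if the strategy makes patients more active and more of them are hurt, the harms comparison should show it. This stands. A reader might infer that the excess is an artefact or a bias that exposure adjustment should remove, and the plan's intention-to-treat aim does not support that. What remains is that the item shows only one side of the balance.
- **Other data exist.** All-cause admissions and emergency visits are collected in both arms, and pain is scored without reference to activity. A reader might infer that the trial has no information on delayed or serious harm, which would be wrong. But the encounters are collected for costing and miss injuries or flares that led to no recorded contact. The pain scores are taken at baseline and 6 months and do not count events in between.
- **The analysis is not fixed for this item.** Calling group the primary independent variable does not rule out other terms, and reporting of adverse events may be set out in the analysis plan. This stands, so the absence of an exposure term is not itself a fault.

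**Conclusion.** The point holds as a fault in how the outcome is defined. As described, the only labelled adverse event outcome omits activity-related harm that appears later and all events outside activity. Net harm cannot be compared between arms from it. That conclusion rests on reading the article's description literally and on no assumed rate.

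The dependence on activity time is a tendency of uncertain size. At an assumed 10% in controls, the immediate arm would show between about 10.9% (R = 1.1) and 14.6% (R = 1.5), given a constant and equal risk per hour. A reader might infer that the outcome must rise with success, or that the window for events is 50% longer in the immediate arm. Neither is established: risk per hour might fall as activity increases, and the ratio of 1.5 applies only to planned activity at month 6. The co-primary outcomes are not affected.

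**What to change.** In both arms, ask at 6 months about any injury, fall, or new or worsened symptom in the last 6 months that needed care or limited usual activity. Add a follow-up tick for whether it occurred during or after physical activity. If the existing form already asks this, correct the description instead.

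For reporting:

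- Compare arms on all such events as the main harms result.
- Give the activity-related subset as a proportion in each arm.
- Present the all-cause hospitalisations and emergency presentations from Healthcare utilisation by arm as safety data.
- Treat any rate per hour of activity as supplementary only. It would divide a 6-month event report by a 7-day recall made after randomisation.

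The cost is one reworded item in English, Arabic and Vietnamese, using the forward translation already applied to the other patient forms, and a minor ethics amendment. No new visit is needed. The downside is that a broader item records more unrelated events.

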##### Healthcare utilisation

This will be collected within New South Wales Health directly from the Activity-Based Management portal. The frequency of all health encounters captured by this system (i.e., hospitalisations, emergency department presentations and non-admitted activities such as specialist consultation and physiotherapy) that participants from both groups have during the 6-month trial period will be collected and costed using routine sources including DRG-based costs from the National Hospital Cost Data Collection [51] for inpatient presentations and Medical Benefits Schedule (MBS) and Pharmaceutical Benefits Schedule (PBS) for outpatient utilisation to inform the trial-based economic evaluation.

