To support the consent process, participant information sheets and consent forms have been translated into Arabic and Vietnamese. To further support informed consent, videos were developed in English, Arabic and Vietnamese by investigators BB and BS, in consultation with the SWSLHD Multicultural Health Service and consumer representatives from the Consumer and Community Participation Committee. The videos explain research concepts, reasons for participating in research and an overview of the study requirements in lay language, adapted for each target community. Access to these videos will be provided via a QR code attached to the participant information sheet on invitation to the study. To support the recruitment and retainment of CALD participants, the district Multicultural Health Service will provide support led by BS. Arabic and Vietnamese speaking multicultural health workers will provide telephone support at initial recruitment, assistance with the completion of survey questions at baseline and 6 months as required, and an additional check-in phone call at 3 months to support engagement with the project. These staff are blinded to physiotherapy team allocation.

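### The records of hospitalisation and emergency presentation already extracted for both arms have costing as their only stated use, while the one adverse-event measure described is a 6-month recall item limited to events during physical activity

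*Protocol article*

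**What the plan says.** **Routine records.** Under Secondary effectiveness outcomes, the Healthcare utilisation section takes encounter frequencies from a NSW Health activity portal, covering "hospitalisations, emergency department presentations and non-admitted activities such as specialist consultation and physiotherapy". The encounters that "participants from both groups have during the 6-month trial period will be collected and costed using routine sources" are, in the section's closing words, "to inform the trial-based economic evaluation". The Economic analysis section then brings utilisation in as a cost component.

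**Adverse events.** The Healthcare evaluation section describes a study-specific questionnaire on impressions of care. One of its questions asks participants "if they experienced any adverse events while participating in physical activity over the last 6 months". The Data collection section excludes impressions of physiotherapy from the baseline assessment, so I read this as a question asked at 6 months only.

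**How the survey is returned.** "follow-up paper-based surveys will be mailed to participants and followed up by blinded research staff if surveys are not returned by mail". Arabic- and Vietnamese-speaking participants are also offered "assistance with the completion of survey questions at baseline and 6 months as required, and an additional check-in phone call at 3 months".

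**Analysis.** The Patient-level effectiveness outcomes section covers primary and secondary effectiveness outcomes. It gives linear regression adjusted for the baseline score for continuous measures and logistic regression for dichotomous ones. The Quantitative analysis section applies GEE with an exchangeable correlation to all models.

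**The concern.** The trial encourages activity in hospital physiotherapy patients, who are expected to include people with cardiac and pulmonary disease, stroke and brain injury. In such a population, the harms of most interest are those serious enough to bring a patient to hospital. The trial will hold those events for both arms, from a source that needs no survey return, no recall and no judgement by the patient about cause. As written, they feed a mean cost per arm, where extra emergency visits can be cancelled by fewer clinic visits.

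The measure that is described as asking about adverse events is narrower in three ways, even if every survey came back:

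- It is confined to events during activity, so a cardiac or respiratory admission that begins at rest falls outside its wording.
- A participant who has died cannot answer it.
- It relies on six months of recall and on the patient linking the event to activity. Patients in one arm are more likely to have been counselled about activity, so that linking could differ between arms. Telling patients only that the study concerns recovery after physiotherapy does not remove this possibility.

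At stake is whether the trial can report an arm comparison of serious events in everyone it recruited.

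**Working it through.** **1. The two sources side by side**

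| | Survey question | Routine records |
|---|---|---|
| Arms and period | Both, 6 months | Both, 6 months |
| Event type | During physical activity only | Any hospitalisation or emergency presentation captured by the portal |
| Needs survey return | Yes | No |
| Needs recall and attribution | Yes | No |
| Stated use | Impressions of care | Costing |

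**2. Is there already an analysis for the records?** The placement under secondary effectiveness outcomes brings them nominally within the between-group analyses. Three things are missing:

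- The secondary effectiveness question in the Background lists activity, function, quality of life, barriers and impressions of care. Neither utilisation nor harm is in it. The only listed question that utilisation serves is cost-effectiveness.
- The section defines a frequency over many encounter types, but no event outcome such as any hospitalisation.
- The continuous-outcome model adjusts for a baseline score, while this section names no period before recruitment. The logistic model needs a dichotomous outcome, and none is defined. No model for counts is given.

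**3. How precise would a comparison be?** The article gives no figure for event rates, so there is none to reproduce. The clustering inputs come from the Sample size section: 15 teams per arm, 10 patients per team (150 per arm) and ICC 0.05.

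The design effect is 1 + (10 − 1) × 0.05 = 1.45. I first checked that this reproduces the planned size, reading the baseline covariance of 0.6 as a correlation and alpha 0.025 as two-sided:

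- adjusted SD = 4.4 × √(1 − 0.6²) = 3.52;
- n per arm = 2 × (2.241 + 0.842)² × 3.52² / 1.5² ≈ 105;
- 105 × 1.45 ≈ 153 per arm, 306 in total, against the stated 300.

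The half-width of a 95% interval for a difference in the proportion with any event, at a common rate p, is

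1.96 × √(2 × p × (1 − p) / 150 × 1.45).

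The event rate is an assumption:

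- p = 5%: 1.96 × √(2 × 0.0475 / 150 × 1.45) = 1.96 × 0.0303 = 5.9 points
- p = 10%: 1.96 × √(2 × 0.09 / 150 × 1.45) = 1.96 × 0.0417 = 8.2 points
- p = 20%: 1.96 × √(2 × 0.16 / 150 × 1.45) = 1.96 × 0.0556 = 10.9 points

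Carrying the ICC of 0.05 over from planned activity to hospital events is a second assumption. At p = 20%, an ICC of 0 (design effect 1) gives 1.96 × √(0.32 / 150) = 9.1 points. An ICC of 0.10 (design effect 1.9) gives 1.96 × √(0.32 / 150 × 1.9) = 12.5 points.

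**The case against.** **A comparison is not excluded.** Utilisation is listed as a secondary effectiveness outcome, frequencies are collected as well as costs, and the analysis section covers such outcomes. This stands, so it would be too strong to say the records will be used only for costing. What remains is that costing is the only use stated, and that no safety role, event definition or fitting model is given.

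**The survey has safeguards.** Blinded staff follow up those who do not return it, and telephone help is available to two language groups. This also stands and reduces loss through non-return. It does not widen the question or let it record deaths.

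**Selective return.** A reader might infer that the sickest patients will be the ones missing. The article gives neither a return rate nor its pattern. If return is the same with and without an event, the observed risk is unbiased. If a true 10% risk met an assumed 70% return with an event and 87% without, the observed risk would be 0.07 / (0.07 + 0.783) = 8.2%. At an assumed 50% and 90% it would be 0.05 / (0.05 + 0.81) = 5.8%. The size depends wholly on assumptions, so the point should not rest on it.

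**Intention to treat.** A reader might also see a conflict with the rule that the main dataset is "constituted of all patients recruited into the study irrespective of what amount of physical activity counselling they received". There is none. That sentence concerns the amount of counselling received, not survey non-response or harms.

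**Safety reporting may be described elsewhere.** A full protocol or SAP may contain it, so the lack of a harms section is not criticised here. The point concerns the purpose this article gives to data it says will be collected.

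**The stakes are modest.** The counselling is brief, patients with a medical contraindication are excluded, and all-cause admissions will largely reflect underlying disease. This is fair. It limits what the comparison can show, but does not make the narrower question a better measure.

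**Conclusion.** The point holds as a low-cost improvement. The described adverse-event question is restricted to events during activity and cannot capture deaths or serious events outside it. The routine records cover hospitalisations and emergency presentations in both arms over the same length of time without depending on the patient's response, but have no stated safety role.

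This follows from the wording of the two sections and needs no assumption about who returns the survey. Nothing in the article is contradictory here, and no planned figure is affected.

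The gain is in coverage more than precision. The interval would be about ±11 points at an assumed 20% event rate, and ±6 to ±11 points over assumed rates of 5% to 20%, with the planned cluster sizes and an ICC of 0.05 carried over. Only a large difference could be ruled out.

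**What to change.** - In Healthcare utilisation, name two safety outcomes over the 6 months: all-cause hospitalisation, excluding the admission during which the patient was recruited, and emergency presentation.
- In Patient-level effectiveness outcomes, state that both will be compared by arm in every recruited patient using the planned GEE approach: a logistic model for any event and a count model for the number of events. Report the intervals, and say that the trial is not powered for these outcomes.
- Report deaths by arm where they are recorded. The article does not say that the portal holds deaths, so this should be checked first.
- Keep the survey question as supporting information on events during activity.

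**Cost.** For hospitalisations and emergency presentations, no new data collection is needed, only an event definition, one table and the models. The recruiting admission has to be identified for patients enrolled as inpatients. Events outside NSW Health, such as private or out-of-state admissions, will be missed, and the report should say so.
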